### Sample size {14}

We based our sample size calculations on the size necessary to detect a clinically significant effect in surgical technique, given that estimates of effect size among gas tamponades are not as precise in the literature and are a secondary purpose of our study. Based on previous results from our center, SSAS is achieved in 92% and 88% of phakic patients undergoing PPV and PPV-SB, respectively, compared to 91% and 90% in pseudophakic patients. We therefore have at most a 4% difference between the treatment groups. In the PRO study reports, SSAS rates differed between PPV and PPV-SB with 83% and 91%, respectively, in phakic patients and 84% and 92% in pseudophakic patients. Based on our previous results, this would yield a small effect size of about 0.13, while this would be approximately 0.25 according to the treatment differences in the PRO study reports. Considering that a treatment difference smaller than what was found in the PRO study could be deemed not clinically significant, we are proposing a total sample size of 560 patients (*n* = 140 per group) which, assuming a 10% drop-off rate, would still allow us to detect an effect size of 0.25 with a power greater than 80% (see Table 3).

**Table 3 Tab3:** Total sample size calculation to detect an effect in the ranges of 0.20 to 0.30 for surgical technique (i.e., PPV and PPV-SB) at various study powers. We are proposing a sample size of 560 patients. Corresponding effect size and power will be achieved for the analysis of gas tamponades (i.e., SF_6_ and C_3_F_8_)

Effect size	Power		
	80%	85%	90%
0.20	784	900	1052
0.25	**504**	**576**	672
0.30	348	400	468

### Recruitment {15}

The clinical team will be responsible for identifying patients with RRD and first presenting the study to them. A dedicated research assistant will then be responsible for screening all patients with RRD presenting to the retina team of the CHU de Québec – Université Laval. When an eligible patient is identified, they will be explained in full the option of participating in the trial and signed consent will be obtained. Given that approximately 350 RRD cases are operated every year at the center, up to 4–5 years of recruitment are anticipated for this study.

### Assignment of interventions: allocation

#### Sequence generation {16a}

Given the large sample size that we aim to achieve, patients will be randomized using simple randomization with computer-generated random numbers at the time of enrollment. A sequence will therefore not be generated in advance. No stratification will be used given that the goal is to allow for the generalizability of the results to any patient presenting with moderately complex RRD.

#### Concealment mechanism {16b}

Because each patient will be allocated to their intervention by simple randomization, a concealment of intervention sequence is not required.

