## Introduction

### Background and rationale {6a}

Two important and common techniques used in the surgical repair of rhegmatogenous retinal detachment (RRD) are pars plana vitrectomy (PPV) and scleral buckle (SB). Both can be used alone or in combination with a gradual shift towards PPV with improvements in technology and technique. Prominent retrospective cohort studies such as the Primary Retinal Detachment Outcomes (PRO) study suggest that a combination of PPV and SB (PPV-SB) has an advantage over PPV alone for phakic and pseudophakic patients [1, 2]. Similarly, a meta-analysis of cohort studies suggests that there may be an increased rate of surgical success without reoperation in patients receiving PPV-SB [3]. However, the few randomized controlled trials (RCT) with small sample sizes (range 30 to 100 patients per group) and heterogenous surgical techniques looking into this question have not found an advantage to additional SB [4–7], and a recent meta-analysis of RCT has also not found an advantage but rather increased myopization, duration of surgery, and postoperative pain following additional SB [8]. In a way to simulate randomization, we performed a propensity score analysis comparing the surgical outcomes of PPV compared to PPV-SB at our center which also showed similar results between both techniques [9]. The discrepancy between the results of non-randomized and randomized studies in this debate is likely due to indication bias, that is, the tendency of surgeons to treat more complex patients using PPV-SB thinking that it will provide them with a better outcome.

In addition to this choice of surgical technique, there is also the use of different gas tamponades which can be of interest. Most commonly, vitreoretinal surgeons use either sulfur hexafluoride gas (SF_6_) or perfluoropropane gas (C_3_F_8_) to maintain the reapproximation of the retina postoperatively, reserving the use of silicone oil to refractory cases where a longer tamponade is needed. SF_6_ remains in the eye for 2 to 3 weeks, while C_3_F_8_ remains in the eye for 6 to 8 weeks. There may therefore be an indication bias to use C_3_F_8_ in more complex cases where a longer tamponade duration is desired. Unfortunately, there are no RCT comparing these two tamponade agents, while studies comparing air and gas tamponades have had mixed results [10, 11].

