#### Strategies to improve adherence to interventions {11c}

The intervention allocation will be determined based on the preoperative appearance of the RRD and will not be permitted to change once in the operating room.

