#### Implementation {16c}

The simple randomization will be done at the time of enrollment by the research assistant who will obtain the signed patient consent.

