### Assignment of interventions: blinding

#### Who will be blinded {17a}

Outcome assessors, investigators, and data analysts will be blinded to the assignment of the interventions and the attributed code in the database until the end. For feasibility reasons, the trial participants and the clinical team including the treating surgeon will not be blinded to the intervention allocation. Blinding of the treating surgeon in relation to surgery technique will not be possible given that they will be responsible for adding the SB, and this will be visible on dilated fundus examination at follow-up given the scleral depression caused by the SB, while blinding to gas tamponade will not be feasible given that the gas bubble will dissipate at a faster rate with SF_6_ compared to C_3_F_8_ on follow-up examinations. As for trial participants, they are operated under local anesthesia with a retrobulbar block and sedation. They can therefore overhear surgeons discussing the next steps with the scrub nurse, deduce the addition of the SB based on duration of surgery, and see the speed at which the gas disappears from their visual field. 

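### Allocation concealment is waived because randomisation is simple, nothing makes the draw final, and one sentence bases allocation on the appearance of the detachment

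*Protocol article*

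**What the plan says.** All references are to the protocol article.

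- **Sequence generation {16a}:** "patients will be randomized using simple randomization with computer-generated random numbers at the time of enrollment". It adds: "A sequence will therefore not be generated in advance". There is no stratification.
- **Concealment mechanism {16b}:** concealment is waived, for this reason: "Because each patient will be allocated to their intervention by simple randomization, a concealment of intervention sequence is not required".
- **Implementation {16c}:** responsibility for the draw is assigned as follows: "The simple randomization will be done at the time of enrollment by the research assistant who will obtain the signed patient consent".
- **Strategies to improve adherence {11c}:** "The intervention allocation will be determined based on the preoperative appearance of the RRD". The same sentence then rules out any change once the patient is in the operating room.
- **Who will be blinded {17a}:** "the trial participants and the clinical team including the treating surgeon will not be blinded to the intervention allocation".
- **Participant timeline {13}:** surgery follows preoperative assessment and allocation within 48 hours (macula on) or 5 days (macula off).
- **Background and rationale {6a}:** the conflict between cohort studies and randomised trials is put down to indication bias, described as "the tendency of surgeons to treat more complex patients using PPV-SB thinking that it will provide them with a better outcome".

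**The concern.** Concealment has two parts. The person enrolling must not know the next assignment, and must not be able to discard, repeat or pre-empt an assignment once it is seen. Unblocked simple randomisation at enrolment secures the first part. Section {16b} treats it as securing both.

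The second part matters here because the trial exists to remove a known preference for adding a buckle in more complex eyes. If some unwelcome draws were repeated, or the patients concerned were never registered, the arms would again differ in complexity. This is the same kind of selection that {6a} blames for the conflicting evidence. Analysis could not reliably undo it, because a discarded draw need leave no record. The sentence in {11c} adds to the problem: read literally, it describes allocation by indication.

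**Working it through.** **Step 1. What the text fixes about the draw.**

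| Safeguard | Where it would appear | What is stated |
|---|---|---|
| Next assignment unpredictable | {16a} | Yes: computer-generated, unblocked, no list |
| Consent and registration complete before the draw | {16c} | Not fixed: the draw is at enrolment, by the assistant who obtains consent; the order is not given |
| One release, no redraw | {16b}, {16c} | Not stated; concealment declared unnecessary |
| Log or locked system | {16a}–{16c}, {19} | Not stated; REDCap is named only for data entry and storage |
| Allocation fixed until surgery | {11c}, {13} | Fixed only from the operating room; up to 48 hours or 5 days are not covered |
| Outside check | {21a}, {23} | No data monitoring committee; no pre-planned audits, though the ethics board may audit |

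Only the first safeguard is in place. Three routes stay open: redrawing, drawing early, and not registering a patient after the draw.

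**Step 2. The basis of allocation.** The abstract (Methods), Trial design {8} and {16a} all say that allocation is random. Section {11c} says that it is determined by preoperative appearance. Both cannot be true.

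**Step 3. Size.** The plan gives no figure on this point, and none can be derived from it. The following only illustrates the scale.

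Inputs from the documents:
- 560 patients less 10% drop-off: 560 × 0.90 = 504, or 252 per arm for each factor. This matches the Table 3 entry for effect size 0.25 at 80% power.
- Significance level 0.05 ({20a}); two-sided is assumed.

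Assumptions not in the documents:
- Half of the eyes are more complex, with SSAS 80%; half are simpler, with SSAS 95%. The mean is 87.5%, inside the 83% to 92% range quoted in Sample size {14}.
- There is no true treatment effect.
- A share *r* of mismatched draws (complex eye to PPV, simpler eye to PPV-SB) is redrawn once.

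Formulas:
- Probability that an eye gets the matching technique: q = 0.5 + 0.5 × r × 0.5 = 0.5 + 0.25r
- SSAS on PPV = (1 − q) × 0.80 + q × 0.95
- SSAS on PPV-SB = q × 0.80 + (1 − q) × 0.95
- Spurious difference = (2q − 1) × 0.15 = 0.075r, in favour of PPV

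Worked case, r = 20%: q = 0.55; PPV 0.8825, PPV-SB 0.8675; difference 0.015. The standard error is √(0.875 × 0.125 × 2/252) = 0.0295. The rejection probability is about P(Z > 1.96 − 0.51) + P(Z < −1.96 − 0.51) = 0.073 + 0.007 = 0.080.

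| r | Spurious difference (points) | Type I error |
|---|---|---|
| 0% | 0 | 5.0% |
| 10% | 0.75 | 5.7% |
| 20% | 1.5 | 8.0% |
| 30% | 2.25 | 11.9% |
| 50% | 3.75 | 24.6% |

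The article uses two yardsticks: a 10-point difference (abstract, Outcomes {12}) and the 8-point cohort difference ({14}). At r = 20% the artefact is 1.5/10 = 15% of the first and 1.5/8 = 19% of the second. In this scenario the arm sizes stay equal (0.5q + 0.5(1 − q) = 0.5), so a count per arm would not reveal it.

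**The case against.** The best defence is that {16b} waives concealment of a sequence, and no sequence exists. With no list and no blocks, nobody can foresee the next assignment. **This stands.** A reader might infer that staff could choose whom to approach by anticipating the allocation; the documents do not support that.

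Second, the preference in {6a} belongs to surgeons, while a research assistant makes the draw. This is a genuine partial safeguard, and the documents ascribe no preference to the assistant. It is only partial: the clinical team first presents the study ({15}), and no separation between the assistant and the unblinded team is described.

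Third, a reader might infer that one person screens, consents and draws. The text does not establish this. Section {26a} gives consent to several designated team members, and {15} says only: "A dedicated research assistant will then be responsible for screening all patients with RRD". Section {16c} joins consent and the draw, and nothing more.

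Fourth, {11c} is probably loose wording. It sits under adherence, and its evident purpose is to fix the plan before surgery. **This largely stands.** It is no evidence that patients are in fact allocated by appearance, but the contradiction still has to be removed.

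Fifth, an article may omit software and audit-trail details, and nowhere does it say that draws are unlogged or repeatable. That would answer a complaint about silence. It does not answer an explicit statement that concealment is unnecessary, and {31c} says that the full protocol is what the journal publishes.

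**Conclusion.** The point holds in this form: {16b} rests on a wrong rationale; as written, nothing makes the assistant's draw final; and {11c} contradicts random allocation. The live routes are redrawing, drawing before consent or registration is complete, and not registering a patient after an unwelcome draw.

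The documents show that these routes are not prevented. They do not show that any has been used, and a reader should not conclude that the trial has reproduced the cohort studies' bias. The size of any bias is unknown. The illustrative range of 0.75 to 3.75 points rests wholly on the assumed SSAS values, the even mix of complexity and the redraw shares. At a 10% redraw share the effect on type I error is small.

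It still merits prompt correction, because selection at allocation cannot be reliably repaired later and recruitment opened in September 2023.

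**What to change.** 1. **Keep simple randomisation.** The sample size and visits do not change.
2. **Rewrite {16b} and {16c}.** State that consent, eligibility and baseline data are recorded irrevocably first. A logged, locked system, for example a randomisation function on the REDCap server already in use, then releases one time-stamped allocation that cannot be redrawn. A pre-generated list is optional: a one-time logged draw closes the gap, and a stored list would itself need concealing.
3. **State that every allocated patient stays in the as-randomised analysis** already planned in {20c}. The wording of {11b} on removing patients from the study should be made consistent with this.
4. **Reword {11c}** so that eligibility, not allocation, is judged on preoperative appearance, and the allocation is fixed from the moment of release and not only from the operating room.

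The cost is a few hours of set-up and a protocol amendment. It can protect only the patients still to be enrolled; recruitment is planned to about July 2027.

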#### Implementation {16c}

The simple randomization will be done at the time of enrollment by the research assistant who will obtain the signed patient consent.

### Assignment of interventions: blinding

#### Who will be blinded {17a}

Outcome assessors, investigators, and data analysts will be blinded to the assignment of the interventions and the attributed code in the database until the end. For feasibility reasons, the trial participants and the clinical team including the treating surgeon will not be blinded to the intervention allocation. Blinding of the treating surgeon in relation to surgery technique will not be possible given that they will be responsible for adding the SB, and this will be visible on dilated fundus examination at follow-up given the scleral depression caused by the SB, while blinding to gas tamponade will not be feasible given that the gas bubble will dissipate at a faster rate with SF_6_ compared to C_3_F_8_ on follow-up examinations. As for trial participants, they are operated under local anesthesia with a retrobulbar block and sedation. They can therefore overhear surgeons discussing the next steps with the scrub nurse, deduce the addition of the SB based on duration of surgery, and see the speed at which the gas disappears from their visual field. 

#### Procedure for unblinding if needed {17b}

Patients who would develop severe complications from their SB (e.g., implant infection or intractable pain) which would require removal of the SB could undergo a second operation to remove it. This would be managed with the clinical team which is also not included in the blinding.

### Data collection and management

#### Plans for assessment and collection of outcomes {18a}

Trained and designated research team members will be responsible for collecting baseline and outcomes data with standardized methods of PHVA measurement and questionnaires. A training session of an hour will be provided to each research team member by a single investigator (MH) to promote data quality.

Regarding the intraoperative description of the RRD, a standardized RRD reporting form will be filled out by each treating surgeon at the time of the operation.

#### Plans to promote participant retention and complete follow-up {18b}

Follow-ups will be scheduled and organized by the research team and regular reminders will be performed to reduce the risk of losses to follow-up. Should a participant discontinue the study follow-ups, the reason for discontinuation, as well as the final BCVA and status of the retina (i.e., attached or detached), will be obtained from an eyecare professional before closing the participant’s study file.

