**Methods:**

Eligible patients with moderately complex RRD will be randomized 1:1 to PPV or PPV-SB and 1:1 to SF_6_ or C_3_F_8_ gas tamponade. Approximately 560 patients will be recruited to be able to detect a difference of around 10% in SSAS rate between the groups. Patients will be followed using multimodal imaging and quality of life questionnaires after the surgical repair until 1 year postoperative. The primary outcome will be a single-surgery anatomic success (SSAS), defined as the absence of reoperation for recurrent RRD in the operating room. Secondary outcomes will be pinhole visual acuity (PHVA) at 8–10 weeks and 6 months, final best-corrected visual acuity (BCVA), final retina status (i.e., attached or detached), time to onset of RRD recurrence, severity and number of complications, and questionnaire results.

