#### Intervention description {11a}

Surgery will be performed under local anesthesia with retrobulbar block (5 to 10 cc of 2% lidocaine without epinephrine and 0.5% bupivacaine in a 1:1 ratio). In all cases, surgery will be performed using a wide-angle viewing system and the Alcon Constellation System (Alcon Laboratories, Inc., Fort Worth, TX) combined with the ULTRAVIT 23-G + or 25-G + vitreous cutter (Alcon).

Pars plana vitrectomy will be performed in a standard fashion starting with central vitrectomy, then by localizing retinal breaks and marking them with endodiathermy. Perfluorocarbon will be used to displace subretinal fluid which will be aspirated at its exit from the retinal break as much as possible to avoid retinal pigment epithelium (RPE) dispersion into the vitreous and maximal vitreous base shaving will be performed in all cases. This will be followed by an air-fluid exchange. The use of cryotherapy to solidify the retina intraoperatively and the use of internal limiting membrane peeling of the posterior pole will be at the discretion of the surgeon. In all cases, laser photocoagulation around retinal breaks, holes, areas of lattice degeneration, and posterior to sclerotomy sites will be done and then a 360° laser retinopexy will be performed at the surgeon’s discretion and consisted of three rows of medium-white burns anterior to the level of the vortex vein, towards and beyond the equator. In cases with SB, after 360° peritomy and dissection in 4 quadrants, a 41-circling band with 3082 sleeves (Labtician Ophthalmics, Oakville, ON, Canada) will be used in all cases and fixed to the sclera at approximately 11.5 mm from the limbus (or 5.5 from the insertion of rectus muscles) using partial thickness scleral tunnel or mattress sutures with 5.0 prolene or nylon performed in four quadrants depending on the surgeon preferences. At the end of the surgery, a gas tamponade will be injected inside the eye, either SF_6_ or C_3_F_8_. The surgical technique at the second surgery, if applicable, will be at the discretion of the treating surgeon.

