### Outcomes {12}

The primary outcome is SSAS defined as freedom from reoperation for recurrent RRD at all follow-up evaluations. Localized recurrences or new tears treated using a laser in the ambulatory clinic will not be considered a failure of the primary surgery but will be noted. We considered a difference of 10% in SSAS to be clinically relevant for this trial and based the sample size calculation on this threshold of chosen efficacy. Secondary outcomes will include PHVA at 8–10 weeks and 6 months, final BCVA, final retina status (i.e., attached or detached), time to onset of RD recurrence, severity and number of complications, and questionnaire results (see Additional file 1). The principal questionnaire was previously used and validated by Potic et al. [12] with additional questions used to specifically assess possible side effects and reductions in quality-of-life associated with the addition of SB and longer-duration intraocular gases. In cases of primary surgery failure, the cause of recurrence (i.e., PVR including epiretinal membrane (ERM) in the macular area causing recurrent RD, new or recurrent retinal breaks) will be reviewed. The extent of PVR at follow-up will also be evaluated. The duration of surgery will also be collected. Number of additional visits and supplementary laser and intraocular pressure treatments will be evaluated. Complications will be graded using the novel Classification of Ophthalmological Complications (COC; see Table 1).

**Table 1 Tab1:** Classification of ophthalmological complications (COC)

Complication grade	Definition
Grade I	Any deviation from the normal postoperative course without the need for modification of planned pharmacological treatment or surgical intervention Allowed therapeutic regimens are as follows: any previous medication, any medication prescribed routinely (i.e., topical antibiotics, glaucoma drops, anti-inflammatory drops, steroid drops, oral pills), artificial tears, hot compresses, and analgesic drugs (Advil/Tylenol only)
Grade II	Requiring change in planned pharmacological treatment with higher frequency or longer duration of drops or the introduction of new drugs (including autologous serum drops); these can include glaucoma drops and steroid drops and the use of oral drugs other than Advil/Tylenol (e.g., Diamox, prednisone). Also includes YAG capsulotomy

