#### Adverse event reporting and harms {22}

All adverse events (defined as a deviation from the ideal postoperative evolution) will be reported in the trial using the novel Classification of Ophthalmological Complications (COC; see Table 1) to be able to capture the severity of all complications.

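### The closing contact for participants who leave follow-up does not ask about reoperation for recurrent RRD, so the primary outcome is left avoidably missing for some of them

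*Protocol article*

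**What the plan says.** All references are to the protocol article.

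- **Leavers.** Section {18b} names three things to obtain before a participant's file is closed: the reason for stopping, "as well as the final BCVA and status of the retina (i.e., attached or detached), will be obtained from an eyecare professional". Reoperation and complications are not among them, and no other section says they are sought for leavers.
- **Primary outcome.** Outcomes {12}: "The primary outcome is SSAS defined as freedom from reoperation for recurrent RRD at all follow-up evaluations". The abstract (Methods) adds the setting: "defined as the absence of reoperation for recurrent RRD in the operating room". Section {12} also says that local recurrences lasered in the clinic do not count as failure.
- **Retina status.** Section {12} lists it among the secondary outcomes: "final retina status (i.e., attached or detached), time to onset of RD recurrence, severity and number of complications, and questionnaire results (see Additional file 1".
- **Second surgery.** Intervention description {11a} foresees it: "The surgical technique at the second surgery, if applicable, will be at the discretion of the treating surgeon".
- **Harms.** Section {22}: "All adverse events (defined as a deviation from the ideal postoperative evolution) will be reported in the trial", graded by the Classification of Ophthalmological Complications (COC). Section {11b} foresees a second operation to remove a buckle.
- **Missing data.** Section {20c} provides for analysis as randomized and multiple imputation.
- **Drop-off.** Sample size {14}: the proposed 560, "assuming a 10% drop-off rate, would still allow us to detect an effect size of 0.25 with a power greater than 80"%.

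**The concern.** The contact is the last chance to learn what happened to the study eye, and it asks for secondary outcomes rather than the primary one. Attached or detached describes the retina on one day. SSAS is about whether a particular event has occurred since surgery. An eye that redetached, was reoperated elsewhere and now lies flat gives the same answer as an eye that never failed.

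Two things are at stake. First, SSAS stays unknown for some leavers when one more question could settle it. If leaving is related to failure, pain or buckle trouble, the missing values need not be balanced between arms. Second, the date of recurrence, needed for the time-to-recurrence analysis, and complications treated elsewhere are not requested either. Buckle removal can arise only with PPV-SB, so a gap there would fall on one side of the surgical comparison.

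**Working it through.** **1. Does the item collected determine the primary outcome?** Set the {18b} answer beside the SSAS definition in {12} and the abstract:

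| Course of the eye | Answer at closing contact | SSAS by definition |
|---|---|---|
| Never redetached | attached | success |
| Redetached, reoperated in the operating room, reattached | attached | failure |
| Redetached, reoperated, detached again | detached | failure |
| Redetached, not reoperated | detached | definition not met, since no reoperation took place |

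Neither answer fixes SSAS. Attached covers both a success and a failure. Detached is strongly suggestive but is still not the defining event.

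**2. The plan's own sample size.** Inputs from {14} and {20a}: effect size 0.25, power 80%, alpha 0.05 (two-sided assumed, since sidedness is not stated).

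- Per level of the surgical factor: 2 × (1.960 + 0.842)² / 0.25² ≈ 251.2, rounded up to 252. Total 504, as in Table 3.
- With 10% drop-off: 504 / 0.90 = 560, as stated.
- Arcsine effect size h = 2·|asin√p1 − asin√p2|: 0.134 for 92% v 88%; 0.241 for 83% v 91%; 0.250 for 84% v 92%. These match the stated 0.13 and approximately 0.25.

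The 560 therefore already allows for 56 participants without an outcome (560 − 56 = 504). The loss of precision is budgeted. What remains is possible bias, and missing data that could have been avoided.

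**3. How many failures could be affected?**

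- Leavers: 560 × 0.10 = 56.
- Failures among them at an assumed SSAS of 90%: 56 × 0.10 = 5.6.
- If leavers fail at an assumed 20%: 56 × 0.20 = 11.2.

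These are upper bounds. They include failures known before the participant left, those treated at the study centre, and eyes still detached at the contact.

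**4. Conditional illustration: what if attached were read as SSAS?** The article does not say this will be done. Suppose 10% leave each arm, every failure among leavers has been reattached, and all are counted as success. Take the cohort-study rates in {14} for phakic eyes (83% PPV, 91% PPV-SB) and 280 per level. The apparent rate is p + 0.10 × k × (1 − p), where k is the failure rate in leavers relative to the arm's own rate.

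| Case | Hidden failures (PPV, PPV-SB) | Apparent rates | Difference | Power |
|---|---|---|---|---|
| None hidden | 0, 0 | 83.0% v 91.0% | 8.0 points | 80.5% |
| k = 1, half hidden | 2.4, 1.3 | 83.9% v 91.5% | 7.6 | 78.2% |
| k = 1, all hidden | 4.8, 2.5 | 84.7% v 91.9% | 7.2 | 75.6% |
| k = 2, all hidden | 9.5, 5.0 | 86.4% v 92.8% | 6.4 | 70.0% |

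With k = 1, all hidden and unequal leaving:

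- 15% PPV and 5% PPV-SB: 0.83 + 0.15 × 0.17 = 0.8555 and 0.91 + 0.05 × 0.09 = 0.9145, a difference of 5.9 points.
- Reversed: 0.8385 and 0.9235, a difference of 8.5 points.

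Under that reading the bias could go either way.

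**The case against.** A reader might infer that the plan will record failed eyes as successes and lose the power shown in step 4. The documents do not support that. Section {12} defines SSAS by reoperation and keeps retina status as a separate secondary outcome, and {20c} sends missing data to multiple imputation. On the plain text, an unknown SSAS is missing, not a success. This part of the objection stands, and the figures in step 4 are only conditional.

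Nor is SSAS unknown for every leaver. Reoperation before leaving is already a recorded failure. The trial has one tertiary centre, with unscheduled visits as needed ({13}) and a research assistant who screens all RRD patients presenting to the retina team ({15}), so a redetachment that returns there can be noticed. Harms treated at the centre can likewise still be captured. This also stands. It narrows the gap mainly to eyes reoperated elsewhere after leaving, for which the documents give no number.

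It would also be too strong to say that imputation cannot cope. The recorded reason for leaving, BCVA and retina status can all inform the imputation model. Only dependence that remains after these are used is a problem.

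Finally, the items on a closing contact might be seen as operational detail that an article condenses. This does not stand. The article does name the items, and those it names do not include the event that defines its primary outcome.

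**Conclusion.** The point holds as a mismatch between what {18b} collects and what {12} defines. Followed as written, the contact secures two secondary outcomes and leaves SSAS avoidably missing for leavers whose reoperation status is not otherwise known. Misclassification would need the further step of reading attached as SSAS, which the article neither takes nor excludes.

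The size is modest: at most about 6 failures among 56 leavers at an assumed SSAS of 90%, or about 11 at an assumed 20% failure rate in leavers, with the true number probably lower. The 56 rests on the plan's drop-off allowance, not on an observed rate. The sample size is not affected. The omission itself is certain; its consequence depends on how many eyes are reoperated elsewhere after leaving. The change is worth making because it costs so little.

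**What to change.** In {18b}, keep the three present items and add to the same contact:

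1. Any operating-room reoperation on the study eye since the last study visit: yes or no, date, and indication (recurrent RRD, or other, including buckle removal).
2. Any complications the professional has on record, to be graded by COC in the trial.

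State there that attached status alone does not establish SSAS, and that SSAS stays missing where reoperation status cannot be learned.

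The setting and indication are needed because {12} and the abstract count only operating-room reoperation for recurrent RRD. The date also serves the time-to-recurrence analysis.

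Cost: slightly more to request at a contact that already takes place, plus the matching case report form fields. The sample size stays at 560. The outside professional may not always hold the surgical details, so some values will remain missing.
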